### Sample size calculation

A priori power analysis has been calculated to determine an adequate sample size for the study. This is a study of independent cases and controls with 1 control per case. Prior data indicate that the exclusive breastfeeding rate at two months of corrected age in preterm infants is 0.53. If the true exclusive breastfeeding rate for intervention mothers is 0.615 (effect size 0.085), we will need to study 531 intervention mothers and 531 control mothers to be able to reject the null hypothesis that the exclusive breastfeeding rates for intervention and control mothers are equal with a probability (power) of 0.8, using the Chi-square test. The Type I error probability associated with this test of the null hypothesis is 0.05. We estimate that the drop-out rate will be 5%, therefore requiring an additional 54 mothers. In total we need a sample size of at least 1116 mothers (I: 558, C: 558). The trial is also powered for the subgroup, low SES mothers. It is estimated that the study period will be 18 months.

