### Randomization process

Mothers who meet the inclusion criteria and who provide consent will be randomized to either the proactive (I) or reactive (C) telephone support group. Each mother will be assigned an identification code when they consent to participate, which will be used at randomization and on all questionnaires. The randomization is done by the BST immediately after discharge (within 24 h) by an automated and secure web-based system administrated independent of the research team. A stratified block randomization will be used, with blocks of 25 high SES and 25 low SES mothers at each participating NICU. The randomization takes place after the BST have collected baseline birth, feeding and socio-demographic data so that the BST or mothers will not be biased by knowing the group assignment. The mothers will be informed of their randomization group immediately following randomization by a telephone call or text message. The study outline is presented in Figure 1.

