### Baseline socio-demographic and birth data collection

Data collection for participating mothers and partners include: educational level, parity, mode of delivery, ethnicity, and smoking habits. Data collection for participating infants include: gender, single or multiple birth, gestational age (GA) at birth, weight at birth, days on ventilator/ Continuous Positive Airway Pressure (CPAP), length of hospital stay, GA and weight at discharge, neonatal sequelae at discharge, breast milk (exclusive, partial, formula milk) and method (breastfeeding, bottle, cup) at discharge. Table 1 details the time points when baseline data will be collected.

**Table 1 T1:** Time schedule for obtaining data on characteristics

**Baseline data**	**All infants admitted at the NICU**	**Trial participants at enrolment**	**Trial participants at discharge**
Date of birth	•	•	
Sex (infant)	•	•	
Gestational age	•	•	
Age (mothers/partners)		•	
Parity		•	
Birth weight		•	
Way of delivery		•	
Single/multiple birth		•	
Educational level (mother)		•	
Ethnicity (mother/partner)		•	
Weight at discharge			•
Date of discharge			•
Days ‘on leave’ before discharge*			•
Infant’s health			•
Parent’s health			•

*In Sweden, parents are sometimes enabled to take their infants home (hours or days), although still admitted to the NICU.

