### Data analysis

All members of the research team will be blind to the group allocation (I, C) throughout the study period and during analyses of primary outcome. Intention-to-treat will be used. This means that analyses will include all randomized mothers in the groups to which they were randomly assigned, regardless of their adherence with the entry criteria, regardless of the treatment they actually received, and regardless of subsequent withdrawal from treatment or deviation from the protocol. To study the differences between intervention group and control group on the primary outcome measure; the proportion of mothers who exclusively breastfeed 8 weeks after discharge, a two-sided Chi - square test will used. The level of significance; p-value is set at p <0.05 in all analyses. The specific statistical analysis used with each outcome variable will be determined by the distribution of the outcome variables. Subgroup analyses will be conducted on SES (low vs. high), parity (primipara vs. multipara), and on GA (very preterm vs. preterm).

Secondary outcomes will potentially be analyzed with a mixed effect model. A mixed effect modeling approach has several advantages when conducting a multicenter study with repeated measurements compared to a conventional analysis. For example, a mixed model, offers an insightful analysis and improved precision by taking into account the different centers in the analysis. In addition, a mixed model does not need complete data from all subjects. The result from a mixed model analysis presents a more accurate estimation of the intervention and standard errors [41].

All qualitative interview data from focus groups with mothers will be recorded, transcribed and analyzed; responses to open questions in the questionnaire will be transcribed. Transcripts will be read by two researchers to independently identify categories and key themes according to qualitative content analysis [42]. The categories and key themes will be discussed at research team meetings and a final version will be agreed. All data from focus groups with staff will be analyzed as with mothers. In addition these will be informed by data from BST meeting and ward observations recorded in a reflective diary. Qualitative data collection and analyses will be performed rigorously and supervised by experienced qualitative researchers.

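### The primary chi-square test is unadjusted although discharge feeding status, the baseline value of the endpoint, is recorded before randomisation: a valid test that gives up precision

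*Protocol article*

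**What the plan says.** **Primary analysis.** The Data analysis section names a two-sided chi-square test for the proportion exclusively breastfeeding at 8 weeks after discharge and names no covariate. The Sample size calculation section uses the same test: "we will need to study 531 intervention mothers and 531 control mothers", "with a probability (power) of 0.8, using the Chi-square test".

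**Baseline feeding.** The Baseline socio-demographic and birth data collection section lists "breast milk (exclusive, partial, formula milk) and method (breastfeeding, bottle, cup) at discharge". The Randomization process section gives the order: "The randomization takes place after the BST have collected baseline birth, feeding and socio-demographic data". Allocation is stratified by NICU and by SES only. The hypothesis under Aim and hypotheses covers mothers who breastfeed exclusively or partially, so this status varies at entry. The planned subgroups are SES, parity and gestational age, and discharge feeding is not among them.

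**Other outcomes.** The text adds "The specific statistical analysis used with each outcome variable will be determined by the distribution of the outcome variables" and "Secondary outcomes will potentially be analyzed with a mixed effect model". Table 2 shows SF-36 at discharge, 8 weeks and 6 months. The other scales (MBFES, SPSQ, MPAS) have no discharge measurement.

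**The concern.** Whether a mother is exclusively breastfeeding at discharge is likely to predict whether she is doing so 8 weeks later. The design does not balance this variable and the primary test does not use it. Two things follow:

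- The variance it explains stays in the error term, so the confidence interval is wider and power lower than the same data allow.
- If the arms differ by chance in the share exclusively breastfeeding at discharge, the estimate moves with that difference and the stated analysis does not correct for it.

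The named test is a decision in the text and not a gap awaiting a SAP. A later plan could adjust only by departing from it.

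**Working it through.** **1. The plan's own figure.** Inputs from Sample size calculation: control rate 0.53 ("the exclusive breastfeeding rate at two months of corrected age in preterm infants is 0.53"), intervention rate 0.615 ("If the true exclusive breastfeeding rate for intervention mothers is 0.615 (effect size 0.085"), two-sided alpha 0.05, power 0.80, ratio 1:1. The mean rate is (0.53 + 0.615)/2 = 0.5725.

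n per arm = [1.960 × √(2 × 0.5725 × 0.4275) + 0.842 × √(0.53 × 0.47 + 0.615 × 0.385)]² / 0.085²
= (1.3713 + 0.5866)² / 0.007225 = 530.6, rounded up to 531.

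This matches the stated figure, and power at 531 per arm is 0.800.

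**2. Variance explained by discharge feeding.** The documents give neither the share exclusively breastfeeding at discharge nor the 8-week rate by discharge status, so both are assumed. Let w be the share exclusive at discharge, and a and b the 8-week exclusive rates in those exclusive and not exclusive at discharge. Each row is set so that wa + (1 − w)b = 0.53.

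R² = w(1 − w)(a − b)² / (0.53 × 0.47), with denominator 0.2491.

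| a | b | w | Numerator | R² |
|---|---|---|---|---|
| 0.60 | 0.40 | 0.65 | 0.0091 | 0.037 |
| 0.65 | 0.25 | 0.70 | 0.0336 | 0.135 |
| 0.75 | 0.25 | 0.56 | 0.0616 | 0.247 |

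**3. Effect on power.** In the linear approximation, adjustment multiplies the variance by (1 − R²), so 531 per arm acts like 531/(1 − R²). Simulation at 0.53 versus 0.615 with 531 per arm (6,000 runs) compared the chi-square test with a test stratified by discharge feeding.

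| R² | 531/(1 − R²) | Power, approximation | Power, chi-square (simulated) | Power, stratified (simulated) |
|---|---|---|---|---|
| 0.037 | 551 | 0.81 | 0.80 | 0.81 |
| 0.135 | 614 | 0.85 | 0.80 | 0.85 |
| 0.247 | 705 | 0.90 | 0.80 | 0.90 |

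Rejection under the null was 4.9% to 5.3% for the stratified test, so the gain does not come from inflated error.

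**4. Chance imbalance.** Take the middle row, with w = 0.70. The standard error of the between-arm difference in that share is √(2 × 0.70 × 0.30 / 531) = 0.0281, so its 95% range is ±1.96 × 0.0281 = ±0.055. With an outcome gap of a − b = 0.40, the unadjusted estimate can move by ±0.055 × 0.40 = ±0.022. That is 0.022/0.085, about a quarter of the target effect.

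**5. SF-36 (secondary).** With a correlation ρ between the discharge and follow-up values (assumption), adjustment multiplies the standard error by √(1 − ρ²). For ρ = 0.3, 0.5 and 0.7 the reduction is 5%, 13% and 29%. The difference detectable with 80% power at 531 per arm falls from 0.172 SD to 0.164, 0.149 and 0.123 SD.

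**The case against.** The strongest reply is that nothing here is wrong. The test is named in advance, the sample size was set for it, and its standard error already allows for chance imbalance in discharge feeding, so type I error is held. At the low end of the assumed range the gain is one or two points of power. All of this stands. The point is an available improvement and does not correct an error.

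A reader might also infer more than the documents support:

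- **That the trial is biased or planned below 80% power.** Randomisation protects against bias, and 531 per arm gives 0.800 on the stated inputs.
- **That the baseline measures are never used.** The Health economic evaluation section derives QALYs from SF-36 through SF-6D, and a repeated-measures mixed model could include the discharge value. What can be said is that the article names neither measure as a covariate in an effectiveness analysis.
- **That choosing tests from distributions causes the lost precision.** The precision is lost through the missing covariate. The sentence on distributions concerns analyst discretion, and it does not reopen the primary test, which is already named.
- **That secondary methods will be chosen after unblinding.** The text does not say so. Distributions can be inspected pooled, and the detail of secondary models commonly belongs in a SAP.
- **That discharge feeding offers the largest possible gain.** The documents contain no figure that would show it.

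**Conclusion.** The point holds as one of efficiency. The primary analysis is fixed as unadjusted, while a pre-randomisation measurement of the endpoint itself is available and unbalanced by design. On the protocol's own rates, adjustment would raise power from 0.80 to about 0.81 to 0.90, a gain of roughly 1 to 10 points. That range rests wholly on the assumption that discharge feeding explains 4% to 25% of the outcome variance.

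The SF-36 part is minor and conditional. Table 2 labels the measurement as baseline at discharge, but the Randomization process section lists only birth, feeding and socio-demographic data as preceding allocation. Randomisation takes place within 24 hours after discharge, so completion of SF-36 before allocation is not established.

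**What to change.** Before any unblinded analysis, replace the chi-square test as the primary analysis with one pre-specified adjusted analysis:

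- Adjust for discharge feeding status (exclusive versus not), NICU and SES, by a regression model or a test stratified on these factors.
- Report a standardised risk difference with its confidence interval, so that the result stays on the scale of the planned 8.5-point difference, and name the variance method.
- Keep the unadjusted chi-square test as a supporting analysis.
- Leave the sample size as it is. The gain then becomes a margin against optimistic assumptions.

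As a minor addition, adjust the SF-36 analysis for its discharge value once it is confirmed that the questionnaire is completed before randomisation.

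The cost is a change of wording in the protocol and analysis plan, recorded as an amendment because the chi-square test is already published as primary. The feeding and stratification data are already being collected, so no further mothers, visits or forms are needed.

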### Health economic evaluation

In the health economic analysis the incremental costs of proactive breastfeeding support will be compared to incremental benefits, in comparison to reactive breastfeeding support [43]. Three kinds of benefits will be considered in the analysis:

•Changes in breastfeeding rate will be linked to decreased risk of diseases and premature death, using best available data on risks of not breastfeeding. Less risk of disease will be transformed to gained quality adjusted life years (QALYs) for each disease’s impact on health care costs and production losses will also be considered.

•Parents’ quality of life, expressed in QALYs, will be measured until 6 months postnatal age, SF-6D based on SF-36 [38,44].

•Use of health care resources of the infant, during the follow up time (6 months) will be measured through questions of the infants’ health and wellbeing, illnesses, visits to health care facilities, apart from normal follow-up visits, in the questionnaire sent to mothers at 8 weeks after discharge and at 6 months PNA.

Costs are measured by the recorded number and duration of telephone calls in both study groups. Number and duration of calls are recorded by the BST in the log book. Cost-effectiveness will be analyzed using a cost-utility analysis. Cost-effectiveness ratio will be expressed as costs per gained QALY [43].

### Ethical considerations

The study has no obvious risks; in the pilot study mothers expressed their appreciation that somebody called. All eligible mothers and their partners who agree to participate in the study will sign a written consent. The mothers and the partners will be informed that participation in the study is voluntary and that they can withdraw at any time and that the questionnaires, answers and results are all anonymous and cannot be linked or influence the medical care they receive any way. The trial is conducted and monitored to minimize harm, if the mother wishes not to be called every day; the mothers have the option to decide when to be called. Log book, questionnaires, and recorded telephone calls are stored in a locked area, not accessible to unauthorized individuals. This study has been approved by the Regional Ethical Review Board, Uppsala 2012-08-15 Dnr: 2012/292.

## Discussion

This paper outlines a RCT designed for mothers of preterm infants to improve breastfeeding rates, mothers’ breastfeeding satisfaction and attachment, and parents’ health and wellbeing. It is designed to be feasible to implement in a NICU, in Sweden and internationally. Results from systematic reviews show that breastfeeding interventions may be more effective than usual care in increasing breastfeeding rates in both the short and long term [45,46]. A recommendation from systematic reviews of breastfeeding intervention is to measure exclusive breastfeeding in research [47]. It is also recommended to conduct an economic analysis to see the cost effectiveness of the intervention and in addition qualitative research to explore the nature of breastfeeding support and mechanisms in how support operates [46]. The intention-to-treat analyses strengthen the inferences from findings as we will include noncompliant mothers and will minimize potential bias. In the design, intervention and control groups will be able to access reactive support which is not standard practice. This strategy reduces the risk of the Hawthorne effect (motivational effect of the interest being shown in them) as all included mothers will be eligible to telephone the BST for support and outcome data will be measured identically for all groups. To reduce the risk for selection bias, very few exclusion criteria will be used, which strengthens the results and generalisability. A strength in this study is that data collection will take place in four hospitals in different counties, which will a) increase the scientific quality by reducing the risk of recruitment bias, b) facilitate participant recruitment within a feasible time, c) enable comparisons of both outcomes and intervention delivery process between different teams and NICU contexts which increases the generalisability to other settings. The process evaluation which combines qualitative interview, observation and call frequency data is carefully designed to illuminate any observed differences in outcomes between the four sites. Care has been taken to minimize both interactions between collection of process evaluation data and either the delivery of the intervention or collection of outcome data. A methodological challenge that may be relevant to this study is unexpected confounders. Although attention has been paid to potential confounders in the design, in which stratified block randomization is used to ensure comparability between groups, unexpected confounders may appear. This study provides a unique opportunity to determine if a proactive telephone support to breastfeeding mothers of preterm infants after discharge from NICU will improve breastfeeding rates, mothers’ breastfeeding satisfaction and attachment, and parents’ health and wellbeing.

## Abbreviations

BST: Breastfeeding Support Team; C: Control; CPAP: Continuous Positive Airway Pressure; GA: Gestational age; I: Intervention; MBFES: Maternal Breastfeeding Evaluation Scale; MPAS: Maternal Postnatal Attachment Scale; NEC: Necrotizing enterocolitis; NICU: Neonatal Intensive Care Unit; SES: Socioeconomic status; WHO: World Health Organization; PNA: Postnatal age; PSI: Parental Stress Index; QALY: Quality Adjusted Life Years; RCT: Randomized Controlled Trial; SF-36: Short Form health survey; SPSQ: Swedish Parental Stress Questionnaire.
